## Abstract

**Introduction:**

Men who have sex with men (MSM) are at increased risk for human papillomavirus (HPV)-related anal cancer and may benefit from targeted vaccination campaigns, but it is unclear whether vaccination of sexually active MSM still prevents anal HPV infections. Protocolised data on vaccine effectiveness (VE) in routine vaccination programmes targeting MSM are limited. We describe a protocol to evaluate the VE against anal HPV-16/18 infections in young MSM.

**Methods and analysis:**

This observational study compares HPV-16/18 infection prevalence between vaccinated and unvaccinated MSM of the same age. We recruit MSM at the Sexual Health Center of Amsterdam, born in 1996–2003, who receive bivalent HPV vaccination (Cervarix) (group 1). Participants complete a questionnaire on demographics and sexual behaviour and provide anal, penile, oral gargle and venous blood samples at months 0 and 24. Adverse events are monitored by a questionnaire 2 weeks post vaccine. Recruitment of group 2, also MSM born in 1996–2003, but not vaccinated against HPV, will start 24 months after recruitment of group 1. The same samples are collected, and the same questionnaire is administered. Anal samples are tested for HPV DNA and, if positive, typed for 25 HPV genotypes including HPV-16/18; serum samples are tested for HPV-16/18 antibodies; other samples are stored for future analyses. Type-specific VE will be estimated as 1–OR, where OR refers to the OR of DNA positivity in group 1 at month 24 versus DNA positivity of group 2 for the respective vaccine types. Recruitment of group 1 started in February 2023 and was completed in June 2024. From February 2025 onwards, group 1 will return for the 24-month visit and recruitment of group 2 will start.

**Ethics and dissemination:**

This study has been approved by the medical ethics committee of the Amsterdam University Medical Center. This protocol presents minimal risk to participants. Findings will be presented to stakeholders in immunisation policy and be disseminated through scientific journals and conference presentations.

**Trial registration number:**

**Clinical Trial Information System 2022-502224-49-00.:**

STRENGTHS AND LIMITATIONS OF THIS STUDYPopulation-level vaccine effectiveness (VE) will be estimated based on a comparison of the human papillomavirus (HPV) prevalence between two comparable groups, using a 2-year buffer period between vaccination delivery at the study clinic and infection status assessment.The study is powered to detect VE against newly acquired anal infections in the presence of persistent infections, for which HPV vaccination is ineffective.Results of this study will provide valuable insights into whether vaccinating sexually experienced men who have sex with men will be beneficial.This study, being observational rather than randomised, may be subject to confounding and VE estimates may be affected despite model-based corrections.The study does not allow estimation of VE regarding persistent anal HPV infections or regarding anal disease.

## Introduction

 Anal cancer incidence and mortality have increased globally over the last three decades among men and women.^1^ The highest incidence of anal cancer is found among men who have sex with men (MSM), with an estimated incidence rate of 19 per 100 000 person-years among HIV-negative MSM and 85 per 100 000 among MSM with HIV.^2 3^ Anal cancer is a serious condition with debilitating treatment sequelae and a 5-year survival ranging from 36% to 83% depending on the stage at diagnosis.^4^ Persistent infection with sexually transmitted high-risk anal human papillomavirus (HPV) is the major cause of anal cancer. Whereas HPV-16 and HPV-18 are known as the most common causative types in cervical cancer, causing ~77% of all cervical cancers,^5^ HPV-16 is by far the most carcinogenic type for anal cancer; 90% of anal cancers are caused by HPV-16.^2 6 7^ In a systematic review, the pooled prevalence of anal HPV-16 infections in individuals over 16 years old was 14% in HIV-negative MSM and 29% among MSM with HIV,^8^ compared with 1.8% among HIV-negative men who have sex with women (MSW)^8^ and 4% in women. Although most anal HPV infections clear within 2 years, clearance rates are lower in MSM when compared with MSW and women, increasing their risk for HPV-related anal cancer.^9 10^

Although some HIV guidelines recommend anal cancer screening for people living with HIV, particularly for MSM with HIV, there is no international consensus on routine anal cancer screening.^11^,^15^ HPV vaccination is seen as the best option for the prevention of anal cancer. Licensed prophylactic HPV vaccines include bivalent, quadrivalent and non-avalent vaccines. All HPV vaccines have been shown to be safe and immunogenic in both men and women.^16^,^19^ Although all vaccines target HPV-16 and HPV-18, the vaccines differ in the number of other HPV types included in the adjuvant used and in cross-protective effectiveness against HPV types not included in the vaccine.^20^ The quadrivalent and non-avalent vaccines also include HPV-6 and HPV-11, which cause the majority of anogenital warts and recurrent respiratory papillomatosis. Non-avalent vaccines additionally target five other oncogenic HPV types (HPV-31, 33, 45–52 and 58), predominantly found in cervical disease. Current HPV vaccines have no therapeutic effect, and therefore, effectiveness of HPV vaccination is highest when given at a young age, that is, before sexual exposure to HPV.

Although most effective when given prior to HPV exposure, HPV vaccination can still be effective when administered at later ages. The per protocol analysis of a vaccine efficacy trial among young MSM with no prior HPV exposure reported 94% efficacy against anal HPV-16 DNA detection at any time and 100% for HPV-18.^21^ Effectiveness among young MSM (ages 16–30 years) with prior HPV exposure is much lower, ranging from 45% to 70% for HPV-16^21 22^ and from 45% to 52% for HPV-18.^23 24^ One study even found a non-significant negative effectiveness against HPV-16 among MSM vaccinated between 18 years and 26 years.^24^ Several studies focused on vaccine effectiveness (VE) for all quadrivalent vaccine-targeted types combined, rather than separately assessing VE for HPV-16 and for HPV-18. Reported effectiveness ranged from 20% to 76% for grouped HPV-6/11/16/18,^2122 24^,^26^ with one study demonstrating no significant effectiveness.^23^ These heterogeneous results may be attributed to differences in study design, such as limiting inclusion criteria to participants with few sexual partners,^21^ excluding HPV-positive individuals at baseline,^21^ relying on self-reported HPV vaccination status^22^,^26^ or including people who had been vaccinated very recently among the vaccinated population.^22 26^ These aspects limit insights into the real-world VE as they can lead to overestimations or underestimations of the effectiveness in populations with prior exposure to HPV. Most studies on VE among MSM concerned the quadrivalent vaccine, few concerned the non-avalent vaccine^24^ and none the bivalent vaccine. A Dutch observational study assessed the impact of bivalent HPV vaccination at 12–16 years of age on anal HPV infections in women aged 18–26 years old, showing a 90% (95% CI: 63% to 97%) reduction in the risk of anal vaccine type HPV infections among vaccinated women compared with unvaccinated controls.^27^

In the Netherlands, regional Public Health Services operate Sexual Health Centres (SHC), where certain key populations can get tested and treated for sexually transmitted infections (STIs) free of charge. These clinics also offer hepatitis B vaccination for target groups, such as MSM. SHCs may also be a logistically feasible setting to reach MSM for HPV-related disease prevention, as individuals disclose their sexual orientation, are at increased risk for acquiring HPV, and many may remain susceptible to HPV exposure throughout their lives. Prophylactic HPV vaccination could potentially prevent future HPV infections within this population. However, it is unclear what the effectiveness of the bivalent HPV vaccine among this target group is. Such evidence is crucial for informing public health strategies; if effective against future infections, targeted vaccination of MSM could significantly accelerate the prevention of anal cancer in this population.^28^

In this study, we aim to assess the VE of the bivalent HPV vaccine against anal HPV-16 and HPV-18 infections in MSM aged 19–26 years visiting the SHC of Amsterdam. The focus on HPV-16 and HPV-18 derives from the fact that the vaccine used in this study is designed to prevent infection from HPV types 16 and 18, and because these are the most important oncogenic types with respect to male anogenital and oropharyngeal cancers: about 90% of anal HPV-related cancers,^6 7^ around 70% of penile HPV-related cancers^29^ and about 90% of HPV-related oropharyngeal cancers are caused by HPV-16/18.^30^ MSM have most likely already had multiple sexual partners and been exposed to HPV. Although these factors may reduce VE compared with vaccination at a younger age, we hypothesise that most individuals who have an anal HPV infection at the time of vaccination will clear this infection, and vaccination will protect them against new infections. Therefore, with this study, we aim to elucidate whether HPV vaccination is effective against future infections in a routine public health setting among this sexually active young MSM population.

## Methods and analysis

### Project status

Recruitment for participants of group 1 began on 1 February 2023 during the Dutch national HPV catch-up campaign; inclusion of 431 participants was completed in June 2024. In February 2025, recruitment of group 2 and 24-month visits of group 1 commenced. The results are expected late 2026.

### Objectives

Here we describe the observational study design to estimate the HPV VE for MSM visiting the SHC of Amsterdam (HPV4M study; Clinical Trial Information System registration number 2022-502224-49-00).

The primary aim of the HPV4M study is to evaluate the direct VE of the bivalent HPV vaccine (Cervarix) against anal HPV-16 and HPV-18 DNA positivity among MSM aged 19–26 years, by comparing the prevalence of anal type-specific HPV infections between unvaccinated MSM and vaccinated MSM, 2 years after vaccination.

Our secondary aims are:

To assess the anal DNA prevalence, the seroprevalence of HPV-16/18 and the determinants of HPV-16/18 infections.To assess the impact of age and number of lifetime sex partners on VE.To assess the serological response after vaccination and factors affecting serological response.To assess how HPV-16/18 anal positivity 24 months after start of vaccination is affected by HPV DNA and antibody status at the moment of vaccination.To assess the proportion of participants who complete the vaccination schedule and the incidence of adverse events (AE) after administration of Cervarix.Finally, to collect samples and data allowing for later estimations of VE against penile and oral HPV infections.

### Study design

The HPV4M study is an observational cross-sectional study among young MSM, with a longitudinal component for the vaccinated group (see figure 1 for schematic representation and timeline).

**Figure 1 F1:**
[figure not shown]
Schematic representation and timeline of HVP4M study. HPV, human papillomavirus. HVP4M, HPV vaccine effectiveness study among MSM.

### Study population

In the Netherlands, the bivalent HPV vaccine is routinely offered to preadolescent girls since 2009 and vaccination was extended to boys in 2022. In 2023, a catch-up campaign was launched to offer the bivalent vaccine to all unvaccinated individuals up to the age of 26 years. The vaccination programme uses a 2-dose schedule in accordance with the Dutch national vaccination programme,^31^ that is, vaccine is given at month 0 and at month 6. People with HIV or other causes of immunosuppression are given an extra dose at month 1.

The HPV4M study was initiated during the national catch-up campaign, but was conducted independently. During the study period, HPV vaccination was available at the same clinic through that national catch-up campaign. The age restriction in the HPV4M study is based on the minimum and maximum age within the national catch-up programme.

Participants are recruited at the SHC of Amsterdam in two phases. During the first recruitment phase, MSM born between 1 January 1996 and 31 December 2003 (aged 19–26 years at the start of the catch-up campaign) attending the SHC and accepting HPV vaccination were invited to participate (group 1). MSM were defined as individuals who were assigned male sex at birth, had not undergone genital gender-affirming surgery, regardless of their current gender identity, and who reported having had sex with partners with a penis in the past 6 months. See table 1 for remaining eligibility criteria. Of note, vaccination leads to seroconversion and very high antibody concentrations in the large majority of people with HIV also.^32^,^36^ Therefore, we did not exclude MSM with HIV from participation. For participants with HIV, CD4 cell counts and HIV viral load data are collected. The expected number of MSM with HIV in this age group is low (<5% of eligible men), so stratified analyses by HIV status will not be feasible. In the analysis, we will conduct a sensitivity analysis excluding people with immunocompromising conditions or the use of immunosuppressive medications or HIV infection.

**Table 1 T1:** Overview of eligibility criteria for group one and group 2, HPV4M study, Amsterdam, the Netherlands, 2023–2026

Inclusion criteria	
Group 1	Group 2
Being male and reporting sex with other men in the preceding 6 months Born between 1 January 1996 and 31 December 2003 (age 19–27 years during inclusion) Attending the SHC in Amsterdam Accepting prophylactic HPV vaccination (as routinely offered within the Dutch catch-up programme) Willing and able to return for a subsequent visit for vaccination Planning to stay in or around Amsterdam over the next 2 years Willing and able to complete an online questionnaire at month 15 Willing and able to return for a month 24 final study visit Providing informed consent	Being male and reporting sex with other men in the preceding 6 months Born between 1 January 1996 and 31 December 2003 (age 21–29 years during inclusion) Attending the SHC in Amsterdam Hypothetically accepting prophylactic HPV vaccination Providing informed consent
**Exclusion criteria**	
Both group 1 and group 2	
Having been vaccinated with one or more doses of any HPV vaccine Not able to read/understand Dutch or English Previous enrolment in the study History of anal cancer or anal intraepithelial neoplasia (AIN) Unlikely to adhere to the study protocol in the opinion of the study physician Allergy to one or more components of the vaccine*	

* We asked patients whether they had ever experienced an allergic reaction to a vaccine or to specific components of any medication.

HPV, human papillomavirus; HPV4M, HPV vaccine effectiveness study among MSM; MSM, men who have sex with men; SHC, Sexual Health Center.

Group 1 will be followed up until 24 months after their first vaccination. In the calendar period that group 1 men return for their 24-month visits, an unvaccinated age-matched control population will be enrolled (group 2) (see figure 1 for schematic representation). Group 2 participants are recruited from the same birth cohorts as group 1 participants, enabling direct comparison of the prevalence of anal HPV-16 and HPV-18 infections between the vaccinated (group 1) and the unvaccinated (group 2) participants. During the recruitment period for group 1, HPV vaccination was available free of charge through the national catch-up campaign for all individuals up to the age of 26 years. Group 2 is recruited after the campaign was concluded, and free vaccination was no longer available. Group 2 participants were asked about their reasons for not having received the HPV vaccine. Participants were eligible for participation in group 2 of the study if they would be willing to get vaccinated if offered the vaccine at enrolment.

Ideally, the study population is representative of all MSM aged 19–26 years attending the SHC at the Public Health Service of Amsterdam, in terms of sexual orientation (eg, sex with only men, sex with both women and men), ethnicity, education, socioeconomic status, number of sexual partners, HPV infection status, presence of coinfections (eg, HIV) and past STIs. However, enrolled participants may differ from this population, as participation depends on willingness and ability to participate in this study. To address this, we will collect information on the above-mentioned variables for both study groups and compare their distribution with that of the reference population from the SHC of Amsterdam.

### Recruitment

All MSM born between 1996 and 2003, attending the SHC of Amsterdam, receive an HPV4M-leaflet and are invited to participate in the study. A SHC nurse explains the study procedures and what participation entails. At this point, the person can either decline, participate immediately after providing an informed consent or provide contact details to be contacted later if they are interested on further consideration. If the person declines, the regular SHC visit continues and the decision is noted, so he will not be approached again. Recruitment also takes place through other channels, that is, by distribution of flyers at the SHC and other places frequented by the target population and via social media. The flyers include a quick response code that allows potential participants to register online through a website of the SHC.

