### Data collection

#### Clinical data

We will obtain clinical data of all participants using both the medical records collected at the SHC and additional online questionnaires. The following data are collected: (1) demographics (age, gender at birth, highest educational level, work status, income, country of birth); (2) general health (including HIV status, STI history, use of alcohol, any drugs and tobacco), (3) sexual behaviour (age of sexual debut; age of anal sex debut; gender of sex partners; number of sex partners in previous 6 months; number of lifetime sex partners; number of anonymous sex partners in previous 6 months; position during anal sex (ie, insertive/receptive), condom use during anal sex).

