When assessing the sample size, we assumed that individuals with vaccine-type antibodies due to prior infections are not susceptible to new vaccine type infections. Some studies have suggested that naturally acquired antibodies after HPV infection reduce the risk of new infections among women.^48^ However, studies also found that the evidence of natural immunity among men was inconclusive^49^ or suggested lack of protection at naturally occurring antibody levels.^50^ It remains uncertain how long natural immunity lasts, if present at all in men, and what the impact of natural immunity is on vaccine-acquired immunity.^51^ We acknowledge that our assumption may be a simplification of the natural immunity. However, we expect that less immunity is likely to improve the statistical power of our study.

Two key challenges of this study are the potential LTFU among the vaccinated MSM (group 1) and the recruitment of a comparable control group. Regarding the latter, we will use age-matching on group level and recruitment in the same setting and time period to ensure a comparable age distribution and recent population exposure between the vaccinated and unvaccinated groups. Furthermore, we will test for comparability on variables like number of sexual partners, STI history, years of sexual activity, etc, and correct for possible confounders in multivariable analyses. The LTFU of group 1 will be minimised by ensuring personal engagement and attention with the participant, combining the follow-up visit with a regular STI visit and sending regular reminders if needed. Furthermore, our sample size of 430 for group 1 accounts for 30% LTFU, which is higher than observed in a similar study at the SHC of Amsterdam.^38^

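### Group 2's outcome swab may be taken at a self-initiated STI-clinic attendance and group 1's at a scheduled month-24 visit, yet reason for visit is not a listed variable; this may inflate VE

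*Protocol article*

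**What the plan says.** Under Recruitment, the approach to men at the clinic is "All MSM born between 1996 and 2003, attending the SHC of Amsterdam, receive an HPV4M-leaflet and are invited to participate in the study". A man may consent and take part at once. The approach is made within ordinary care: "If the person declines, the regular SHC visit continues and the decision is noted, so he will not be approached again". There are other routes: "Recruitment also takes place through other channels, that is, by distribution of flyers at the SHC and other places frequented by the target population and" social media, with online registration, and a man may also leave his details to be contacted later. Under Procedures and interventions, group 2 has a single visit, so enrolment and outcome sampling coincide.

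For group 1, the Study population section says: "Group 1 will be followed up until 24 months after their first vaccination". Table 1 requires such men to be "Willing and able to return for a month 24 final study visit". The Discussion adds that loss to follow-up will be limited by, among other things, "combining the follow-up visit with a regular STI visit and sending regular reminders if needed".

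The primary contrast is group 1 at month 24 against group 2. The Discussion bases comparability on group-level age matching and "recruitment in the same setting and time period to ensure a comparable age distribution and recent population exposure between the vaccinated and unvaccinated groups". Clinical data lists demographics, "general health (including HIV status, STI history, use of alcohol, any drugs and tobacco", and sexual behaviour, including total and anonymous partners in the last 6 months, position and condom use. Neither that list nor the comparability variables named in the Discussion include reason for visit, symptoms or partner notification.

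**The concern.** The event that leads to the outcome swab differs between the groups. In group 2 it can be the man's own decision to attend an STI clinic. In group 1 it is a date fixed by the first dose. Recruiting in the same clinic and calendar period equalises place and time, but not what brought the man in that day.

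A man who attends with symptoms, or because a partner was diagnosed, is likely to have had recent contact with an infected partner, and that may also raise his chance of current anal HPV DNA. Two men with equal partner counts can differ in this respect. If such men make up a larger share of group 2's outcome swabs than of group 1's, the control prevalence is raised relative to the vaccinated prevalence and VE is overstated. The error would favour the vaccine in a study meant to inform immunisation policy.

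**Working it through.** **Plan's own figures (Sample size calculation).** Control prevalence is 13.9% for HPV-16 and 11.3% for HPV-18; expected month-24 prevalence in group 1 is 6.2% and 4.6%.

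- HPV-16: OR = (0.062/0.938)/(0.139/0.861) = 0.0661/0.1614 = 0.409, so VE = 59%.
- HPV-18: OR = (0.046/0.954)/(0.113/0.887) = 0.0482/0.1274 = 0.378, so VE = 62%.
- The stated 264 and 284 per group reproduce exactly with the two-sided, continuity-corrected two-proportion formula at 80% power.

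**Inputs that the documents do not give (assumed).**
- s2, the share of group 2 outcome swabs taken when the man attended for symptoms or notification: 20–50%.
- s1, the same share in group 1: 5–10%.
- R, the odds ratio of HPV-16 positivity for such men against others: 1.3–2.

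**Formulas.** Let b be the prevalence in men not so affected, and q the prevalence with odds R·b/(1−b).
1. Solve (1−s2)·b + s2·q = 13.9% for b.
2. Group 1 prevalence under no vaccine effect: p = (1−s1)·b + s1·q.
3. Apparent VE under no effect = 1 − odds(p)/0.1614.
4. Apparent VE when the true VE is 59% = 1 − 0.409 × odds(p)/0.1614.

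**One case in full.** s2 = 40%, s1 = 10%, R = 1.5 gives b = 11.92% and q = 16.87%. Check: 0.6 × 11.92 + 0.4 × 16.87 = 13.9. Then p = 0.9 × 11.92 + 0.1 × 16.87 = 12.41%, with odds 0.1417. The ratio is 0.1417/0.1614 = 0.878, so VE under no effect is 12.2%. A true 59% appears as 1 − 0.409 × 0.878 = 64%.

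**Results for HPV-16, before any adjustment.**

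| s2 | s1 | R | VE shown, no effect | VE shown, true 59% |
|---|---|---|---|---|
| 20% | 10% | 1.3 | 2.8% | 60% |
| 20% | 5% | 1.3 | 4.1% | 61% |
| 40% | 25% | 1.5 | 6.2% | 62% |
| 40% | 10% | 1.5 | 12.2% | 64% |
| 40% | 10% | 2 | 20.7% | 68% |
| 50% | 10% | 2 | 26.1% | 70% |
| 50% | 5% | 2 | 29.2% | 71% |
| 30% | 20% | 1.3 | 2.7% | 60% |
| 30% | 20% | 1.15 | 1.4% | 60% |

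Crossing all the assumed ranges gives about 3–29% under no effect and about 60–71% for a true 59%. The 40%/25% row and the last two rows lie outside those ranges and show how the bias falls when the groups are more alike or the association is weaker.

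**Second check, with the exposure defined as any care visit.** Assume 80% of group 2 swabs are taken at care visits with a prevalence ratio of 1.25. Control prevalence is then 13.9% × (0.8 × 1.25 + 0.2) = 16.7%. If 0%, 25%, 50% or 80% of group 1 month-24 visits are also care visits, VE under no effect is 19%, 13%, 7% or 0%. The direction is the same, and under no effect the bias vanishes when the shares are equal.

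**The case against.** A reader might infer that care visits raise prevalence in the control group alone. The article does not support that. The Discussion plans to combine group 1's follow-up with regular STI visits, so some group 1 outcome swabs will also be taken at care attendances. A reader might also infer that most group 2 men are swabbed while attending for care. The article gives no split between men approached at the clinic and those who come through flyers, social media or later contact. Attendance also includes routine and PrEP visits, which are not the problem here.

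The suspected mechanism is partly measured. Recent and anonymous partners, position, condom use and STI history are collected, the same questionnaire is used at both outcome visits, and variables with a known effect on HPV risk enter the model. Anal HPV DNA also changes slowly: the article cites 24-month clearance of 65% for prevalent HPV-16, so prevalence reflects many months of exposure and the trigger of one visit may add little. The article concedes that residual confounding may occur.

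Finally, this is a condensed article. The questionnaires are in an appendix that is not shown, clinic records are a data source, the adjustment set is defined by a rule, and the list of comparability variables is open-ended. It cannot be said that visit reason is unrecorded, only that the article does not list it.

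All of this limits the size of the bias and the confidence in it. It does not remove the asymmetry: partner counts do not show whether a recent partner was infected, and whether the two groups' shares are similar cannot be checked unless reason for visit is available.

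**Conclusion.** The point holds as a possible bias in favour of the vaccine that the stated safeguards do not address. Group 2's outcome swab may coincide with a self-initiated attendance, group 1's is scheduled, and the variable that would show whether this matters is not listed. It is neither an error of fact nor a contradiction in the plan.

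The size rests wholly on assumption. Under the ranges above, the unadjusted effect is about 3–29% apparent VE for a vaccine with no effect, and about 1 to 12 points added to a true 59%. The planned adjustment would remove part of that. With similar shares in the two groups it is small: about 3% under no effect at 30% against 20% and an odds ratio of 1.3. The change is cheap enough to be worth making despite this uncertainty.

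**What to change.** For each outcome swab (group 1 at month 24 and group 2 at its single visit), obtain the reason for attendance in three classes: symptoms or partner notification; routine or PrEP check; study visit only. Take it from the SHC record where it is held there, and otherwise from one questionnaire item. Then:

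- report its distribution by group;
- include symptoms or partner notification in the adjusted VE model regardless of whether the groups differ significantly on it;
- repeat VE after excluding such men from both groups, as a sensitivity analysis.

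The cost is one variable, some loss of precision in the restricted analysis, and possible missing data for visits already made, since group 2 recruitment and the month-24 visits began in February 2025.
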